**Study population**

Multidisciplinary and participatory workshops conducted to ascertain local health priorities in the urban slum of Belén demonstrated that intestinal parasites were among the top-five health priorities and that targeted health hygiene education interventions were required [1]. In fact, in a recent survey we conducted in Belén, we found 86% of Grade 5 school children infected by at least one STH species (*Ascaris*=60.4%, *Trichuris*=77.9%, and hookworm=21.2%) [2].

We have obtained current information on the number of children enrolled in Grade 5 in schools of Belén, Peru. For efficiency purposes, only schools with a minimum enrolment of 10 boys and 10 girls in Grade 5 will be considered eligible. Eighteen schools, totalling more than 1438 students, are therefore considered eligible to participate in this trial.

*Inclusion criteria*

- Girls and boys enrolled in Grade 5 in one of the 18 eligible schools in Belén.
- Informed written consent obtained from the parents or legal guardian of the child.
- Verbal assent from child.

*Exclusion criteria*

- Parents (or guardians) refusing participation of their child.
- Child who refuses to participate.

[figure not shown]

Figure 1: Flowchart of the cluster-randomized controlled trial

**Health hygiene education intervention**

Lack of knowledge on the transmission and prevention methods of STH infections is common factor in affected population groups of Latin America [27]. Therefore, the specific objectives of the health hygiene education intervention are:

i) To implement a gender-specific health hygiene education strategy which will result in a sustainable intervention that encourages the pro-active role of both teachers and students.

ii) To encourage changes in attitudes and practices with the aim of keeping the level of parasite infection low, through increased knowledge.

iii) To identify modifiable gender-specific behavioural and social determinants which favour the acquisition and transmission of STH infections to inform prevention activities.

Workshops will be organized for and by Grade 5 teachers to train them on the health hygiene education strategy. The education material will be provided by the Pan American Health Organization (in Spanish) and will be adapted to the local culture. The health hygiene education intervention will take into account the gender-specific perceptions, values, social constructs, and beliefs of students and teachers relevant to STH infections in order to maximize behavioural changes. After the workshop, Grade 5 teachers will be able to implement the health hygiene education intervention in their classroom and engage their students. Bi-monthly visits with the teacher by our research team and once monthly with the class will be performed to monitor the application of the education program during the 4-month follow-up period. Specifically, the intention of the health hygiene education program is to modify key gender-specific modifiable behavioural determinants that have been shown to be associated with STH infections from our review of the literature:

i) Not using soap for hand washing [28-30]

ii) Not hand washing (no reference to the use of soap) [31-33]

iii) Eating unpeeled or unwashed fruits [31, 34]

iv) Walking barefoot [30, 33]

v) Open air defecation [33-35]

vi) General unhygienic behaviours [36]

**Measurements**

Weight of the child will be measured using a portable flat scale (seca 869, seca corp., Baltimore, MD) and a mobile stadiometer (seca 217, seca corp., Baltimore, MD) will be used to measure their height. Individual risk factors, potential confounding variables, level of knowledge on STH transmission, and behavioural determinants will be measured using an interviewer-administered questionnaire at baseline. After the 4-month follow-up period, the same questionnaire will be re-administered.

Stool specimens will be obtained in small plastic containers at baseline and at the end of the 4-month follow-up period by trained research personnel. Trained technologists will use the Kato-Katz method to examine the specimens for the presence, species and intensity of STH eggs [37]. This technique is the preferred method for assessment of the prevalence and intensity of intestinal parasitic infections in the field [4, 38]. The technologists will be blinded to the group assignment.

Data collection activities during fieldwork will be regularly supervised. Measurement bias will be kept to a minimum by ensuring calibration of study instruments (balance and scale), quality control assessments, and daily review of completed questionnaires. At each assessment, the coordinator will check all completed forms immediately after data collection at the end of each day. Entries on the questionnaires will be checked and if discrepancies or unclear answers appear, a discussion and explanation of the question and eligible answers will take place to avoid making errors the next day. Corrections will be made, if warranted. These types of errors should be kept to a minimum, as there will be a pre-testing phase with all interviewers to ensure correct data collection procedures and records. The consistency of the microscopic readings will be verified both during the examination and afterward as follows. The consistency of egg counting will be evaluated among the laboratory technologists using standard quality control methods [38]. The laboratory supervisor will read 10% of the slides of each microscopist without prior knowledge of the results. In the case of a discrepancy larger than 10%, the two readers will discuss the slides and further slides will be examined to avoid repeated errors. It should be noted that trained microscopists from our previous study will perform the examinations. They have an excellent performance record.

**Sample size justification**

Based on our survey of schools in Belén, 18 schools are eligible and have already demonstrated an interest in participating in the study. They have a total of 1438 students enrolled in Grade 5 (Table 2). Power calculations are based on the formula for logistic regression with a single binary covariate (i.e. the education intervention) and the Wald test was used as the basis for computations [39]. Based on our past parasitological Belén school surveys a response rate of 80.6% is expected [2]. A 5% loss to follow-up is also assumed during the 4-month period. Thus, we estimate a sample size of 1101 participating students, distributed in the 18 schools.

In addition, the power calculations must take into account within-school clustering. The intraclass correlation coefficient (ICC) represents the proportion of the total variance that is accounted for by between-cluster rather than within-cluster variation and can be used to calculate the Effective Sample Size (ESS). Because we could not find any reported ICC of within-school clustering of STH re-infection in the literature, we re-analysed the original database of [name] et al. [2], which contained the parasitological results of 1074 Belén students, and calculated the within-school ICC of STH prevalence (as an estimation of ICC of re-infection rates). The ICC was calculated using STH prevalence as the outcome and the school as the grouping factor, while adjusting for age, sex, and the school ecological zone (floodplain or upland). The obtained ICC had a value of 0.028 which resulted in an ESS of 412 and an associated design effect of 2.7. Power was estimated assuming that 50% of children will be exposed to the intervention and that the re-infection rate in the control group will be 49.5%. The latter is based on the reported 3-month re-infection rate of Malaysian school-children treated with albendazole [40]. Thus, the proposed study has good power (80.3%) to detect a moderate effect (i.e., OR=1.75) and has an excellent power (93.4%) to detect a strong effect, corresponding to an OR of 2.00.

The efficacy of the deworming program will be determined using a sub-sample of 300 previously infected children. Assuming the most conservative value of a 50% cure rate, this sample size of 300 will result in precise species-specific cure rates estimated with a maximum 95% confidence interval of ± 5.7%. No within-school clustering is assumed for cure rates because variables affecting cure rates are intrinsic to the parasites and the hosts themselves, not the schools.

Table 2: Number of Grade 5 students enrolled in 2007 and 2008 in the 18 eligible schools located in the Belén district of Iquitos, Peruvian Amazon

| **School name** | **Nb. grade 5 students 2007** | **Nb. grade 5 students 2008** | **Nb. classrooms** |
| --- | --- | --- | --- |
| Bagazan | 42 | 49 | 2 |
| Santo Cristo Bagazan | 134 | 125 | 4 |
| Diego Natal Juan | 109 | 87 | 3 |
| Ruy Guzmán Hidalgo | 181 | 160 | 5 |
| Participación | 147 | 116 | 3 |
| Enry Herve Linares Soto | 26 | 24 | 1 |
| Ramón Castilla | 266 | 203 | 6 |
| Sara Alicia Saberbein Pinedo | 175 | 186 | 5 |
| Sachachorro | 65 | 56 | 2 |
| San Lucas | 104 | 113 | 3 |
| Violeta Correa | 47 | 53 | 2 |
| Sagrada Familia | 53 | 79 | 2 |
| Isla Iquitos | 34 | 32 | 1 |
| San José | 43 | 25 | 1 |
| San Francisco | 43 | 42 | 2 |
| Nuevo Liberal | 63 | 37 | 1 |
| La Victoria de Jesús | 33 | 31 | 2 |
| Nuevo Campeón | 25 | 20 | 1 |
| **Total** | **1590** | **1438** |  |

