**Methods**

**Study design**

A prospective cluster-randomized controlled trial design will be used (Figure 1). Schools will be randomly allocated to one of the two arms using a stratified randomization technique (by school size). Because the total number of students enrolled in Grade 5 varies from 20 to more than 200 per school, the stratified design will ensure a balanced proportion of children in each of the two arms. A simple baseline questionnaire will be administered to all Grade 5 students to collect information on gender-specific risk factors and to evaluate the level of knowledge regarding STH infections. Each child will be weighed and measured (for anthropometric measures), and a stool specimen will be collected and examined for STH eggs (to estimate STH infection rates and intensity). The health hygiene education intervention will begin immediately after the routine deworming program in schools in the intervention arm. Schools in the control arm will follow their standard curriculum. (These schools will be offered the health hygiene education intervention after the 4-month follow-up period.)

Two weeks after the deworming, an efficacy assessment will be undertaken in a sub-sample of 300 previously-infected children (ie. Stool specimens will be collected to estimate cure rates for each STH. This is needed to provide a correction factor in the data analyses.). At the end of the 4-month follow-up study period, the baseline questionnaire will be re-administered to all children in both arms, the children will be weighed and measured, and re-infection rates will be assessed by collecting a stool specimen from each child. Absenteeism rates, based on routine school records, will be assessed from baseline to the end of the follow-up period. An intention-to-treat analysis will be used to compare outcomes in the two arms.

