**Planned statistical analyses**

All children in both arms will be included in the analysis (i.e., an intent-to-treat analysis). Preliminary analyses will include descriptive statistics (means and standard deviations for continuous variables; frequencies for categorical variables) for all measurements in each intervention group separately. Gender-disaggregated data will be presented in tables, whenever pertinent.

Multivariate analyses will be used to compare the post-deworming (at 4-months) STH re-infection rates between the two groups. To account for the within-school clustering, hierarchical (random effects) logistic regression models will be used [41]. The model will include important confounding variables such as gender, sex, age, school ecological zone, as well as any baseline characteristics that may not be balanced between the two groups. Subgroup analysis will be performed for boys and girls separately as well as for each of the three helminth species studied (*Ascaris*, *Trichuris*, and hookworm).

All statistical tests will be two-sided and a 0.05 level of significance will be used throughout for determination of statistical significance. Point estimates of the intervention effect with 95% confidence intervals will be presented to demonstrate the precision of the study results.

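### The stated power of 80.3% and 93.4% treats the 18 schools as equal in size; with the school sizes in Table 2 and the planned random-effects model it is about 74-75% and 89-90%

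*Protocol*

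**What the plan says.** The Protocol, Sample size justification, starts from the eligible schools: "They have a total of 1438 students enrolled in Grade 5 (Table 2". It expects 80.6% of students to respond and 5% of those to be lost, which leaves 1101 children in 18 schools. For clustering it reports that "The obtained ICC had a value of 0.028 which resulted in an ESS of 412 and an associated design effect of 2.7". The power method is described thus: "Power calculations are based on the formula for logistic regression with a single binary covariate", with a Wald test, half the children exposed and 49.5% of controls re-infected. The conclusion is that "the proposed study has good power (80.3%) to detect a moderate effect (i.e., OR=1.75"), and 93.4% for an odds ratio of 2.00.

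The same document shows that the schools differ greatly in size. Study design says that "the total number of students enrolled in Grade 5 varies from 20 to more than 200 per school". Table 2, titled in part "Number of Grade 5 students enrolled in 2007 and 2008 in the 18 eligible schools", gives all 18 sizes; the 2008 column runs from 20 to 203 and sums to 1438. Size is used to stratify the randomization, but the power calculation makes no visible allowance for it.

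Planned statistical analyses fixes the test level ("All statistical tests will be two-sided and a 0.05 level of significance will be used throughout") and a hierarchical (random effects) logistic regression to handle clustering by school.

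**The concern.** For a given number of children and schools and a given ICC, unequal schools carry less information than equal ones. Children added to a large school share that school's effect, so each adds less than a child in a small school. In 2008 the six largest schools (113, 116, 125, 160, 186 and 203) hold 903 of the 1438 children, or 63%. A design effect calculated at the mean school size ignores this and makes the ESS too high.

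The stated power is the protocol's quantitative justification for its primary comparison. All 18 eligible schools are already included, so no further schools are in reserve to absorb a shortfall. If the figure is too favourable, a reader of a null result will set the chance of having missed an odds ratio of 1.75 at about 20%, when on the plan's own inputs it is about 25%.

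**Working it through.** **Inputs, all from the Protocol.** 1438 enrolled, 80.6% response, 5% loss, 18 schools, ICC 0.028, equal allocation, control rate 49.5%, odds ratios 1.75 and 2.00 (Sample size justification); two-sided 0.05 (Planned statistical analyses); the 18 enrolments for 2008 (Table 2).

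**1. Reproduce the stated figures.**
- N = 1438 × 0.806 × 0.95 = 1101; mean per school m = 1101/18 = 61.2.
- Equal-cluster design effect: 1 + (m − 1) × ICC = 1 + 60.17 × 0.028 = 2.68; ESS = 1101/2.68 = 410. The protocol gives 2.7 and 412. An ESS of 412 corresponds to an ICC of 0.0278, which rounds to 0.028.
- Wald power = Φ(|ln OR|/SE − 1.96), with SE² = 1/[(ESS/2) p0(1 − p0)] + 1/[(ESS/2) p1(1 − p1)]. For a protective odds ratio of 1/1.75, p1 = 0.359. At ESS 412, SE = 0.201, ln 1.75/SE = 2.78, and power is 79.4%. For 1/2.00, p1 = 0.329 and power is 92.6%.
- Taking the odds ratio above 1, or using a two-proportion formula, gives 79.6-80.1% and 92.8-93.3%. All are within about a point of the stated 80.3% and 93.4%.

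The protocol does not name its design-effect formula. The equal-cluster formula reproduces both 2.7 and 412; neither of the two unequal-cluster formulas below does.

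**2. Measure how unequal the schools are.** The 2008 sizes have mean 79.9 and standard deviation 56.4 (divisor 18), so the coefficient of variation is 0.71. Scaled to a total of 1101, they run from about 15 to 155.

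**3. Recompute under near-efficient weighting, which the planned random-effects model approximates.** Each school contributes m_i/[1 + (m_i − 1) × 0.028]:
- smallest school: 15.3/1.40 = 10.9;
- largest school: 155.4/5.32 = 29.2, so about ten times the children bring less than three times the information;
- sum over 18 schools: ESS = 365, and design effect = 1101/365 = 3.01.

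At ESS 365 and an odds ratio of 1.75, SE = 0.214, ln 1.75/SE = 2.62, and Wald power is 74.5%.

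**4. Lower figure, for an analysis that gives every child equal weight.** 1 + [(1 + CV²) m − 1] × ICC = 1 + (1.498 × 61.17 − 1) × 0.028 = 3.54; ESS = 1101/3.54 = 311.

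| Basis | Design effect | ESS | Wald power, OR 1.75 | Wald power, OR 2.00 | OR with 80% power |
|---|---|---|---|---|---|
| Stated in the protocol | 2.7 | 412 | 80.3% | 93.4% | not stated |
| Equal schools, reproduced | 2.7 | 412 | 79.4% | 92.6% | 1.76 |
| Table 2 sizes, efficient weights | 3.01 | 365 | 74.5% | 89.4% | 1.82 |
| Table 2 sizes, equal weight per child | 3.54 | 311 | 67.6% | 84.1% | 1.92 |

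Across both directions of effect and both power formulas, the third row spans 74.5-75.2% and 89.4-90.2%. The 2007 enrolments give 74.4-75.1% at an odds ratio of 1.75, so the year does not matter.

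**5. A separate sensitivity.** With 18 schools, a t reference on 16 degrees of freedom gives about 69% at ESS 365 and an odds ratio of 1.75. It also lowers the equal-school case, to 74%, so it is a small-number-of-schools effect and not part of the unequal-size error.

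**The case against.** **The inputs are themselves rough.** The ICC is openly a proxy, taken from prevalence rather than re-infection, and the control rate comes from a 3-month study while this trial runs 4 months. With the Table 2 sizes and efficient weights, an ICC of 0.022 would bring power back to 80%, and 0.035 would lower it to 68%. A shift of 0.006 in the ICC therefore matters as much as the error described here. This stands as a reason not to over-read any single figure. It does not rescue the stated one: the protocol adopts 0.028, and 80.3% does not follow from 0.028 with these schools. The uncertainty also runs in both directions.

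**Stratification and covariates.** Randomization is stratified by school size, and the model adjusts for covariates, for which the calculation gives no credit. Stratification balances the number of children between arms, but does not restore the information lost when many children share one school. The protocol quantifies no gain from covariates, so none can be counted.

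**Little depends on the number.** All eligible schools are in, so the calculation describes a fixed sample rather than setting one, and the planned 95% confidence intervals will show the precision achieved. This is right, and it limits how serious the point is.

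**A stronger reading to avoid.** A reader might take the equal-weight formula and infer that power at an odds ratio of 1.75 is only 68%. That formula fits an analysis weighting each child equally; the plan specifies a random-effects model, which weights schools close to efficiently. The 68% is a lower figure, not the expected one. Nor do the documents support converting the ICC of 0.028 to a larger value at a 49.5% rate, since they do not say on which scale it was estimated.

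**Conclusion.** The point holds at a modest size. The ESS of 412, the design effect of 2.7 and the two power figures rest on equal schools, which Table 2 contradicts. Under the planned model, power is about 74-75% at an odds ratio of 1.75 (about 5 points lower on the same formula) and 89-90% at 2.00 (about 3 points lower). The odds ratio with 80% power is about 1.82 rather than 1.75.

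This rests on four assumptions: the protocol's ICC and control rate are taken as given; response and loss are the same in every school; the random-effects model weights schools near-efficiently; and the equal-cluster formula, which is inferred from the numbers, is the one that was used. The direction of the error does not depend on the weighting.

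It should be fixed as the restatement of a stated power. Randomization, the analysis model and the test level are unaffected, and the trial would still have good power for its strong effect.

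**What to change.** In Sample size justification, recompute from the 18 school sizes in Table 2 and replace the current figures with a design effect of about 3.0, an ESS of about 365, power of about 74-75% at an odds ratio of 1.75 and 89-90% at 2.00, and an odds ratio of about 1.82 for 80% power. Name the formula and say that it allows for unequal school sizes under the random-effects analysis.

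Optionally, add two labelled sensitivities: the equal-weight formula as a lower bound (design effect 3.5, ESS 311, power 68% and 84%), and a t reference on 16 degrees of freedom (about 69% at an odds ratio of 1.75 with ESS 365).

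The cost is one rewritten paragraph and a less favourable power statement. Enrolment, the number of schools and the analysis stay as they are.

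### The stated maximum of ±5.7% for species-specific cure rates counts all 300 children for every species; on the protocol's own prevalences the maximum is about ±5.9% (Trichuris), ±6.8% (Ascaris) and ±11.4% (hookworm)

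*Protocol*

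**What the plan says.** The Study design section states that two weeks after deworming "an efficacy assessment will be undertaken in a sub-sample of 300 previously-infected children". It gives the aim as follows: "Stool specimens will be collected to estimate cure rates for each STH". It adds that the result is needed as a correction factor in the data analyses. Species-specific cure rates are also secondary objective iii.

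The Sample size justification repeats the number: "The efficacy of the deworming program will be determined using a sub-sample of 300 previously infected children". The precision statement rests on two assumptions, "Assuming the most conservative value of a 50% cure rate" and "No within-school clustering is assumed for cure rates". From these it concludes that "this sample size of 300 will result in precise species-specific cure rates estimated with a maximum 95% confidence interval of ± 5.7" per cent.

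The species mix comes from the Study population section. In the earlier Belén survey "we found 86% of Grade 5 school children infected by at least one STH species", with Ascaris at 60.4%, Trichuris at 77.9% and "hookworm=21.2" per cent.

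**The concern.** A child who did not carry hookworm at baseline cannot be cured of it, so the hookworm cure rate has only the hookworm-positive children in its denominator. The same holds for the other two species. Being previously infected means carrying at least one of the three, and neither section that describes the sub-sample sets a quota per species or says 300 per species. Unless every sampled child carries all three species, a half-width computed on 300 cannot be the maximum for each of them.

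At stake is how far the cure rates can be relied on, above all for hookworm. A child who is egg-positive at four months may have been re-infected or never cured, and the cure rate is the planned means of telling these apart on average. The denominators are set when the 300 are chosen, so a reader who trusts ±5.7% has no reason to look at the hookworm count until it is too late to raise it.

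**Working it through.** **Inputs, all from the protocol**
- Sub-sample: 300 infected children, no species quota (Study design; Sample size justification).
- Cure rate 50%, 95% confidence, no clustering (Sample size justification).
- Prevalence: any species 86%, Trichuris 77.9%, Ascaris 60.4%, hookworm 21.2% (Study population).
- Enrolment 1438, response rate 80.6% (Sample size justification).

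**1. Reproduce the stated figure.** Half-width = 1.96 × √(p(1 − p)/n). With p = 0.5 and n = 300: 1.96 × √(0.25/300) = 5.66%, which rounds to ±5.7%. The arithmetic is right for a denominator of 300.

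**2. Expected denominators.** Every carrier of a given species is infected with at least one, so the expected share of carriers among infected children is species prevalence / 0.86.

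| Species | Expected carriers among 300 | Half-width at 50% cure |
| --- | --- | --- |
| Trichuris | 300 × 0.779/0.86 = 272 | 1.96 × √(0.25/272) = ±5.9% |
| Ascaris | 300 × 0.604/0.86 = 211 | 1.96 × √(0.25/211) = ±6.8% |
| Hookworm | 300 × 0.212/0.86 = 74 | 1.96 × √(0.25/74) = ±11.4% |

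For hookworm, 11.4/5.7 = 2.0. A Wilson interval gives ±11.1%, so the choice of interval matters little.

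**3. Chance variation in the hookworm count.** A binomial draw of 300 with probability 0.212/0.86 has a 95% range of 60 to 89 carriers. At those ends the half-width is 1.96 × √(0.25/60) = 12.7% and 1.96 × √(0.25/89) = 10.4%.

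**4. Could 300 per species have been meant?** Expected hookworm-positive participants: 1438 × 0.806 × 0.212 = 246. Sampling all of them gives 1.96 × √(0.25/246) = ±6.2% to ±6.3%, still above 5.7%. To reach ±5.7% for hookworm at 50% cure needs 0.25 × (1.96/0.057)² = 296 hookworm-positive children. At the survey's mix that means 296/(0.212/0.86) ≈ 1,200 infected children, against an expected 1438 × 0.806 × 0.86 = 997.

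**5. Sensitivity to the cure rate (hookworm, n = 74).** 80% cure: 1.96 × √(0.16/74) = ±9.1%. 90% cure: 1.96 × √(0.09/74) = ±6.8%. The half-width falls to 5.7% only at a cure rate of about 93%.

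**6. Sensitivity to a finite population correction.** The protocol uses none. If one were applied, with 300 of about 997 infected participants sampled, every half-width would shrink by √(1 − 300/997) = 0.836: 5.66% → 4.7% on all 300, Trichuris 5.9% → 5.0%, Ascaris 6.8% → 5.6%, hookworm 11.4% → 9.5%. The gap between the all-300 figure and each species keeps the same ratio.

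**The case against.** The best case for leaving this alone is that it concerns one precision sentence for a sub-study. The gap is trivial for Trichuris (5.9% against 5.7%) and modest for Ascaris (6.8%), and only the least common species is materially affected. The ±11.4% is also a worst case: it assumes 50% cure, an unstratified draw and a species mix carried over from an earlier survey. If cure is high, or if only the trial's own children are the target, the interval is narrower.

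Most of this stands as a limit on severity. It does not rescue the figure. The protocol itself chose 50% as the conservative value and called the result a maximum, so the comparison has to be made on that basis. A finite population correction would bring Trichuris and Ascaris under 5.7%, but the protocol's own figure would then be 4.7%, and hookworm would still be at about 9.5%.

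A reader might infer that the primary analysis is compromised, because the cure rates supply a correction factor. The documents do not support that. The Study design section speaks only of the data analyses in general. The re-infection model under Planned statistical analyses mentions no correction factor, and the species comparisons appear there as subgroup analyses. The effect on any re-infection result cannot be worked out from the text.

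**Conclusion.** The statement is wrong as written: the formula is applied correctly, but to a denominator that no species-specific cure rate will have. On the protocol's own prevalences and its 50% assumption, the maximum half-widths are about ±5.9% for Trichuris, ±6.8% for Ascaris and ±11.4% for hookworm. The shortfall is negligible, moderate and about twofold respectively. Reading the text as 300 per species does not help, because the trial can expect only about 246 hookworm-positive participants.

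The conclusion assumes that the 300 are drawn without regard to species and that the survey mix holds at baseline. It takes the protocol's assumption of no clustering as given. The ±11.4% is an upper bound at 50% cure and should not be read as the precision that will be observed. The point bears on secondary objective iii and on the unspecified correction factor. It leaves the primary sample size and power calculation untouched. It should be fixed, but nothing in the main design depends on it.

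**What to change.** Replace the single figure with the expected precision for each species on its own denominator: about 272, 211 and 74 children, giving half-widths of up to ±5.9%, ±6.8% and ±11.4% at 50% cure for Trichuris, Ascaris and hookworm. State that this assumes an unstratified draw at the survey's species mix. The cost is one sentence, and that is enough to correct the document.

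Optionally, if the team wants a tighter hookworm estimate, the 300 can be drawn from the baseline stool results with hookworm-positive children over-represented. Choosing previously infected children already requires those results, and the Measurements section has the stools read by species. For example, 150 of the roughly 246 expected positives would give 1.96 × √(0.25/150) = ±8.0% for the same 300 stools. The per-species figures above would then no longer apply. Ascaris and Trichuris precision would need recalculating from the co-infection pattern, which the protocol does not give. Sampling weights would be needed for the pooled rate and for the Ascaris and Trichuris rates, since co-infection may be related to cure. Any such rule must be set before the two-week collection.

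### The planned cure-rate precision of at most ±5.7% assumes no within-school clustering, for a reason that does not imply independence

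*Protocol*

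**What the plan says.** Protocol, Sample size justification, plans the cure-rate estimate as follows: "The efficacy of the deworming program will be determined using a sub-sample of 300 previously infected children". The precision is worked out "Assuming the most conservative value of a 50% cure rate", and the species-specific rates are said to be "estimated with a maximum 95% confidence interval of ± 5.7" percent. The justification for using no design effect is that "No within-school clustering is assumed for cure rates because variables affecting cure rates are intrinsic to the parasites and the hosts themselves", as opposed to the schools.

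The same section treats the primary outcome differently. It says that power must allow for within-school clustering. Having found no published ICC for re-infection, it takes one from the earlier Belén survey of STH prevalence, adjusted for age, sex and ecological zone: "The obtained ICC had a value of 0.028 which resulted in an ESS of 412 and an associated design effect of 2.7".

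Cure rates and egg reduction rates are secondary objective iii. Study design says that the two-week efficacy assessment supplies a correction factor for the data analyses. Planned statistical analyses names hierarchical models for the re-infection comparison and does not mention cure rates.

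**The concern.** Clustering is a matter of whether children in one school resemble each other, not of where the cause of the resemblance lies. A determinant can belong entirely to the host or the parasite and still be shared within a school. The protocol gives an example: infection is a host-parasite outcome, and its ICC stays at 0.028 after adjustment for age, sex and zone.

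The two calculations are also handled inconsistently. With no ICC available for re-infection, the protocol borrowed one. With none available for cure, it set the value to exactly zero on a verbal argument.

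At stake is the stated precision of a secondary objective. Because ±5.7% is offered as a maximum, readers will take it as a ceiling on the uncertainty about drug efficacy.

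**Working it through.** **Inputs.** n = 300, cure rate 0.50, 18 schools and ICC 0.028 (for STH prevalence), all from Sample size justification. School sizes are the 2008 enrolments in Table 2 (total 1438). Prevalences are from Study population: any STH 86%, *Ascaris* 60.4%, *Trichuris* 77.9%, hookworm 21.2%. The ICC for cure is an **assumption**; 0.01 to 0.05 is shown, with 0.028 as a reference only.

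**1. The protocol's figure.** 1.96 × √(0.25/300) = 5.66%. The ±5.7% is therefore the simple binomial figure with design effect 1, and its arithmetic is right.

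**2. Design effect, schools standing for a wider population.**
- Equal numbers per school: m = 300/18 = 16.7, and DE = 1 + (m − 1) × ICC. At 0.028, DE = 1 + 15.67 × 0.028 = 1.44.
- Numbers in proportion to Table 2: the squared enrolments sum to 172,130, so Σm²/300 = 300 × 172,130/1438² = 25.0. At 0.028, DE = 1 + 24.0 × 0.028 = 1.67.

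**3. Half-width, 5.66% × √DE.**

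| Assumed ICC for cure | Equal numbers: DE, half-width | In proportion to Table 2: DE, half-width |
| --- | --- | --- |
| 0 | 1.00, ±5.7% | 1.00, ±5.7% |
| 0.01 | 1.16, ±6.1% | 1.24, ±6.3% |
| 0.028 | 1.44, ±6.8% | 1.67, ±7.3% |
| 0.05 | 1.78, ±7.6% | 2.20, ±8.4% |

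The protocol does not say how the 300 are spread over schools. At ICC 0.028, drawing them equally from nine schools would give ±7.8%, and from six ±8.7%.

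**4. Species-specific denominators.** The figure is called species-specific, but not every infected child carries each species. If the 300 have the species mix of the earlier survey (an assumption), the expected number with a species is 300 × prevalence/0.86.

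| Species | Expected number | No clustering | ICC 0.028, equal | ICC 0.028, Table 2 sizes |
| --- | --- | --- | --- | --- |
| *Ascaris* | 211 | ±6.7% | ±7.7% | ±8.2% |
| *Trichuris* | 272 | ±5.9% | ±7.0% | ±7.5% |
| Hookworm | 74 | ±11.4% | ±11.9% | ±12.2% |

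For hookworm the denominator matters far more than clustering, so one overall figure would mislead whatever ICC is used.

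**The case against.** **The target may be these schools only.** All 18 eligible schools are to take part. If cure is wanted only for children in this trial and all 18 schools are sampled, schools act as strata and between-school variation adds nothing. At ICC 0.028 the half-width is then 5.66% × √(1 − 0.028) = 5.6%. A finite-population correction for about 950 to 1,000 infected participants lowers it to roughly ±4.6 to 4.7%. This stands, and it limits the point to inference beyond these schools or to a sub-sample from only some of them. The Executive summary wants results to inform programmes in Peru and similar endemic areas, which suggests wider inference, although it does not say so for cure rates.

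**The ICC is borrowed.** The 0.028 describes prevalence, which depends on exposure. Cure is conditional on being infected and treated. A reader might infer that cure clusters at 0.028; the protocol does not show that. It shows only that an outcome rooted in host and parasite is not thereby independent of school.

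**The text is about planning.** A reader might also infer that the reported cure-rate intervals will ignore clustering. The sentence fixes planned precision. It does not give the method for the reported interval, and that method may be in an analysis plan that is not shown.

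**The consequence is modest.** Even 0.028 adds only 1.1 to 1.6 points at 50% cure. The half-width at that ICC is back within the claimed figure once cure exceeds about 78% (equal schools) or 82% (Table 2 sizes). This also stands, but a figure presented as a maximum has to hold at the least favourable cure rate, which the protocol itself took to be 50%.

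**Conclusion.** The point holds as a fault in planned precision. The reason given for zero clustering does not support it, and ±5.7% is not a maximum if the cure rates are to speak for drug efficacy beyond these 18 schools. Any positive ICC then pushes the half-width above the computed 5.66%. Over an assumed ICC of 0.01 to 0.05 it is about ±6.1% to ±8.4% at 50% cure, and ±6.8 to 7.3% at the protocol's own value for infection. The direction is firm under that target; the size rests on an ICC for cure that the protocol does not give and on an allocation of the 300 that it does not state.

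A reader might go further and conclude that understated uncertainty passes into a corrected re-infection estimate. The document does not establish this: Study design mentions a correction factor without defining it, and the model in Planned statistical analyses does not mention one. Primary power is unaffected, since it already carries a design effect of 2.7.

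**What to change.** 1. Delete the sentence that assumes no within-school clustering of cure rates.
2. State that the 300 children will be spread over all 18 schools, and how many come from each.
3. Report species-specific cure rates and egg reduction rates with marginal intervals that allow for school, for example a school-level bootstrap or a cluster-robust variance with a small-sample correction. A random-intercept logistic model is less suitable: its cure rates are conditional on school unless averaged over schools, and about four hookworm cases per school (74/18) would barely support it.
4. Replace ±5.7% with a range over plausible ICCs for each species, using the number expected to be infected with that species. State whether the target is these schools or a wider population.

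The same 300 stool specimens serve. The cost is a small sampling instruction, some wording on the analysis, and a stated precision that is slightly less favourable overall and clearly less favourable for hookworm, where the denominator is the main reason.
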